**Abstract**

Objectives

To evaluate the effectiveness of Hydroxychloroquine Phosphate/Sulfate (200 mg orally 8 hourly thrice a day for 5 days) *versus* oseltamivir (75 mg orally twice a day for 5 days) *versus* Azithromycin (500 mg orally daily on day 1, followed by 250 mg orally twice a day on days 2-5) alone and in combination (in all seven groups), in clearing the coronavirus (COVID-19) nucleic acid from throat and nasal swab and in bringing about clinical improvement on day 7 of follow-up (primary outcomes).

Trial Design

An adaptive design, set within a comprehensive cohort study, is chosen because it permits flexibility in this fast-changing clinical and public health scenario. The randomized study will be a multicenter, multiarm, multistage, randomized controlled trial with a parallel design. An observation only cohort will emerge from those not consenting to randomization.

Participants

Eligible will be newly diagnosed patients, either hospitalized or in self-isolation, without any comorbidities or with controlled chronic medical conditions like diabetes mellitus and hypertension. Participants of any gender or age group having tested positive for COVID-19 on Real-Time qRT-PCR (Quantitative Reverse Transcription PCR) will be invited to take part in study at twelve centers across nine cities in Pakistan. Those pregnant or lactating, severely dyspneic or under respiratory distress, already taking a treatment, and with serious co-morbidities like liver or kidney failure will be excluded.

Intervention and Comparator

A total of seven comparator groups will be formed: Each drug (Hydroxychloroquine Phosphate/Sulfate, Oseltamivir and Azithromycin) given as monotherapy (three groups); combinations of each of two drugs (three groups); and a final group on triple drug regimen.

Main Outcomes

The laboratory-based primary outcome will be turning test negative for COVID-19 on qRT-PCR on day 7 of follow-up. The clinical primary outcome will be improvement from baseline of two points on a seven-category ordinal scale on day 7 of follow-up.

Randomization

Participants will be randomized, maintaining concealment of allocation sequence, using a computer-generated random number list of variable block size into multiple intervention groups.

Blinding

Computerized allocation to treatment group will be done upon adding participants demographic details and confirmation of informed consent. Neither physician nor participants will be blinded.

Sample Size

This is an adaptive design and parameters for formal sample size calculation in a new disease of a previously unknown virus are not available. Then the sample size and power analysis are indicative for review at each stage of adaptive design. In a standard two-arm, head-to-head trial, the sample size would have been as follows: in order to detect a difference in the laboratory-based primary outcome of 10% (assuming a 50% of participants receiving Hydroxychloroquine Phosphate/Sulfate turn test negative at day 7 and expected rates in comparator groups of 60%), at a significance level 5% and a power of 90%, a sample size of approximately 520 subjects in each group will be required. This sample size will be enough to detect a small-medium difference (Cohen’s d 0.3, a significance level 5% and a power of 90%) in the clinical primary outcome.

Trial Status

By July 03, 2020, the trial had recruited a total of about 470 participants across 12 centers after approval from National Bioethics Committee and Drug Regulatory Authority of Pakistan. Recruitment started on April 20, 2020. The recruitment is expected to continue for at least next three months subject to review of data monitoring and safety board as estimated in Version 1.7.

Trial Registration

Prospectively registered at **clinicaltrials.gov ID: NCT04338698**

*The full protocol is attached as an additional file, accessible from the Trials website (Final_1.7_Plain)*

*The study protocol has been reported in accordance with the Standard Protocol Items: Recommendations for Clinical Interventional Trials (SPIRIT) guidelines and this is a PDF version of protocol 1.7 without citations for specific sections nested at the top (SPIRIT_Nested,pdf)*

Key Words

SARS-CoV-2, Hydroxychloroquine, Azithromycin, Oseltamivir, multi-center, adaptive, randomization

Declarations

Authors declare no financial or any competing interests

Ethics Approval

The proposed study is approved by National Bioethics Committee of Pakistan **(notification attached)** and IRBs at majority of participating sites. Remaining sites have endorsed the ethics approval of both University of Health Sciences Lahore and National Bioethics Committee (NBC).

Certified that this trial has received ethical approval from the appropriate ethical committee as described above

Consent for publication

Applicable through this submission

Availability of data and materials

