***Methods: Participants, interventions, and outcomes***

**4 PARTICIPANTS**

***SPIRIT Guidance: Study setting***

*9 Description of study settings (eg, community clinic, academic hospital) and list of countries where data will be collected. Reference to where list of study sites can be obtained*

Study sites comprise major public-sector tertiary care health facilities and Covid-19 field hospitals being setup within province of Punjab. Hospitals in other provinces and federal areas will also be invited for participation. Households with self-isolating individuals could also participate in the study. A list of hospitals with confirmed participation has been attached as **Annex 3.**

***SPIRIT Guidance:*** *Eligibility criteria*

*10 Inclusion and exclusion criteria for participants. If applicable, eligibility criteria for study centers and individuals who will perform the interventions (eg, surgeons, psychotherapists)*

Eligible will be newly diagnosed patients without any comorbidities or those with controlled chronic medical conditions, e.g. diabetes mellitus and hypertension. Participants of either gender or age group having tested positive for COVID-19 on qRT-PCR (Quantitative Reverse Transcription PCR) will be invited to take part. Participants who are pregnant or lactating, are already taking any treatment, under respiratory distress or severely dyspneic, have liver and kidney failure will be excluded from the study. Each participant will undergo baseline investigation i.e., liver function tests, renal function tests, urinalysis, and Complete Blood Count; at the time of enrollment. However, diagnostic facilities and hospital admission criteria could vary across cities. A case report form (CRF) has been developed for this proposal and **attached** at the end of this document.

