***Inclusion Criteria***

1. Confirmed SARS-CoV-2 (COVID-19) infection by a positive test result
2. Either gender
3. Symptomatic for example fever, dry cough, myalgias

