***Exclusion Criteria***

1. Confirmed absence of SARS-CoV-2 (COVID-19) infection by a negative test result
2. Have chronic conditions such as heart disease, liver and kidney failure
3. Ongoing respiratory distress or severely dyspneic
4. Pregnant or currently lactating female
5. Immunocompromised, atopic and/or systemic disease(s)
6. On other antiviral drugs
7. History of allergy to any of the drugs to be administered in this study

Both recruitment and administration of study drugs will be carried out by any member of the site investigation team. All site teams have been trained accordingly.

***SPIRIT Guidance:*** *Interventions*

*11a Interventions for each group with enough detail to allow replication, including how and when they will be administered*

Participants will be divided into seven intervention groups (A to G) and eighth group (H) comprising non-consenting individuals observed for supportive care (Figure 1). Study physician(s) will administer three drugs as monotherapy (to three intervention arms), in combination regimen of any of the two trial drugs (to three additional arms), and seventh intervention arm comprising all three drugs. The three drugs with respective dosages are - Hydroxychloroquine Phosphate/Sulfate (200 mg orally 8hr thrice a day for 5 days) versus oseltamivir (75 mg orally twice a day for 5 days) versus Azithromycin (500 mg orally daily on day 1, followed by 250 mg orally twice a day on days 2-5)

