***SPIRIT Guidance:***

*11b Criteria for discontinuing or modifying allocated interventions for a given trial participant (eg, drug dose change in response to harms, participant request, or improving/worsening disease)*

Study physicians will observe, interview, and report any suspected adverse drug reaction (sADR) to their unit teams and subsequently to electronic data entry module. “A sADR is an unwanted or harmful reaction experienced following the administration of a drug or combination of drugs under normal conditions of use and is suspected to be related to the drug”. In case of sADR, the participant will be informed of discontinuation of given therapy until resolution of symptoms is observed and/or receipt of corresponding investigations (Electrocardiogram, Hepatotoxicity, Nephrotoxicity, Myelotoxicity) confirm the suspicion or otherwise. Findings will be conveyed to participant and recorded on electronic data module. A written report of any confirmed episode will also be immediately submitted to Drug Regulatory Authority of Pakistan (DRAP) on its prescribed proforma **(attached** as sample). Any decision to modify the study protocol or drug dosage will be informed by aggregated data on ADRs and Drug Regulatory Authority is a statutory forum to exercise these decisions (if warranted) through pre-notified National Data Safety & Monitoring Board (NDSMB). Irrespective of sADR, the study participants reserve the right to withdraw their informed consent at any point of time throughout recruitment period.

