***SPIRIT Guidance: Implementation***

*16c Who will generate the allocation sequence, who will enrol participants, and who will assign participants to interventions*

Randomization sequence was created using Sealed Envelope Ltd 2019 and was stratified by study center and age using random block sizes of 28 and 42 sizes into seven treatments (11). Before randomizing, recruiting physician will confirm eligibility and obtain written informed consent from the participant. Upon entering participant’s demographic details in the IT module, a unique patient ID for the said center and treatment arm would be allocated automatically meaning the recruiting physician has no control over assigning intervention.

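### Patients of any age are eligible but each drug has one fixed milligram regimen, so an eligible child is allocated the same dose as an adult

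*Protocol*

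**What the plan says.** Age is left open in two places. The Abstract (Participants) invites "Participants of any gender or age group having tested positive for COVID-19". The eligibility text under section 4, Participants (SPIRIT item 10) has "Participants of either gender or age group having tested positive for COVID-19". The numbered lists do not narrow this. The three inclusion criteria are a positive test, either gender and symptoms. The seven exclusion criteria cover a negative test, chronic organ disease, respiratory distress, pregnancy or lactation, immune or systemic disease, other antivirals and drug allergy.

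Dosing is stated once per drug, with no age or weight bands. Under Interventions (SPIRIT item 11a): "The three drugs with respective dosages are - Hydroxychloroquine Phosphate/Sulfate (200 mg orally 8hr thrice a day for 5 days", followed by oseltamivir 75 mg twice daily for 5 days, and azithromycin 500 mg on day 1 then 250 mg twice daily on days 2 to 5. The Abstract and the Primary Objective repeat the same regimens.

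On changing the dose, SPIRIT item 11b says: "Any decision to modify the study protocol or drug dosage will be informed by aggregated data on ADRs". At enrolment, SPIRIT item 16c says the "recruiting physician will confirm eligibility and obtain written informed consent from the participant", after which the IT module takes demographic details and allocates the arm automatically.

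**The concern.** The two rules are compatible with each other but unsafe in combination. Open age eligibility needs doses that vary with age or size, and a single fixed dose needs a population for which it is suitable. The protocol has neither a lower age limit nor a dose rule.

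What is at stake is participant safety before the first dose. The smallest eligible participants would receive a multiple of the adult dose per kilogram, and in one arm this applies to three drugs at once. The point does not touch the sample size, the power or the analysis.

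**Working it through.** **Is there a rule anywhere that would stop this?** The relevant provisions, side by side:

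- *Eligibility (Abstract; section 4; inclusion and exclusion lists).* Any age; no age or weight item among the three inclusion and seven exclusion criteria.
- *Interventions (item 11a).* One milligram regimen per drug.
- *Modification (item 11b).* Therapy stops after a suspected reaction, so only after exposure. Dosage changes are made for the trial as a whole, through the regulator and the NDSMB. Nothing adjusts an individual's dose by age or size.
- *Concomitant care (item 11d).* Site physicians have discretion over care outside the protocol, not over the allocated study dose.
- *Randomization (items 16a, 16c) and analysis (item 20).* Age is a stratification factor and an analysis subgroup, never a limit.
- *Recruitment (item 15).* Home-isolated patients may be recruited by phone and have medicines delivered, so the directly observed dosing at study sites (item 11c) does not cover them.

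None of these sets a dose or a limit by age before treatment starts.

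**Inputs from the protocol**

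- Hydroxychloroquine: 200 mg × 3 = 600 mg/day; over 5 days, 3,000 mg.
- Oseltamivir: 75 mg × 2 = 150 mg/day; over 5 days, 750 mg.
- Azithromycin: 500 mg on day 1, then 250 mg × 2 = 500 mg/day; in total 500 + 4 × 500 = 2,500 mg.
- Arms containing a given drug: 1 monotherapy + 2 pairs + 1 triple = 4 of 7.

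**Assumed inputs.** The protocol gives no body weights. The weights below are illustrations only.

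**Formula.** Dose per kg per day = daily dose ÷ weight. Because the daily dose is constant, the ratio to a 70 kg adult is 70 ÷ weight for every drug.

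| Assumed weight | Hydroxychloroquine (mg/kg/day) | Oseltamivir (mg/kg/day) | Azithromycin (mg/kg/day) | Ratio to 70 kg | Ratio to 50 kg |
|---|---|---|---|---|---|
| 70 kg | 600/70 = 8.6 | 150/70 = 2.1 | 500/70 = 7.1 | 1 | – |
| 50 kg | 600/50 = 12 | 150/50 = 3 | 500/50 = 10 | 70/50 = 1.4 | 1 |
| 30 kg | 600/30 = 20 | 150/30 = 5 | 500/30 = 16.7 | 70/30 = 2.3 | 50/30 = 1.7 |
| 20 kg | 600/20 = 30 | 150/20 = 7.5 | 500/20 = 25 | 70/20 = 3.5 | 50/20 = 2.5 |
| 10 kg | 600/10 = 60 | 150/10 = 15 | 500/10 = 50 | 70/10 = 7 | 50/10 = 5 |

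**Effect on the trial's statistics.** None. The protocol's figure of about 520 per group (50% against 60%, two-sided 5%, 90% power) reproduces as 519 with the usual two-proportion formula without continuity correction, and it does not depend on this point.

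**The case against.** The strongest reply is that children were probably never meant to be enrolled. Controlled diabetes and hypertension, the pregnancy and lactation exclusions and the WHO quality-of-life questionnaire all suggest an adult setting, and the any-age wording may be loose drafting for no upper limit. That is plausible, but no text states a lower limit, and a site applying the criteria as written would find a child eligible.

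Second, harm is not shown. The weights are assumed, the documents give no per-kilogram limit, and the sevenfold figure needs a 10 kg participant. This stands: the multiples describe relative exposure, and the 10 kg row is an illustrative extreme.

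Third, there are safeguards: physician confirmation of eligibility, observed dosing at sites, stopping after a suspected reaction, and an independent board that can halt an arm. They lessen the risk. But the physician confirms against criteria with no age item, and the others act during or after dosing.

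Fourth, an age floor does not equalise dose per kilogram among adults. This is true: an assumed 40 kg adult still gets 70/40 = 1.75 times the 70 kg value. The concern, however, is with children, where the ratio is larger and a floor removes it.

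Finally, the protocol text describes consent by the participant and gives no guardian or assent route. The consent form is not available here and may contain one, so the conclusion does not rest on this.

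**Conclusion.** The point holds. The stated eligibility and the stated dosing together give a child the same milligram dose as an adult, of up to three drugs, and no rule in the protocol prevents it before the first dose. Per-kilogram exposure would be 2.3 to 7 times that of a 70 kg adult, or 1.7 to 5 times that of a 50 kg adult, for assumed weights from 30 down to 10 kg.

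The protocol gives no age distribution, so the number of minors among the roughly 470 recruited by July 03, 2020 is unknown and may be zero. Recruitment was expected to continue for at least three more months under the same wording. This is a safety and eligibility defect that is cheap to correct. Eligibility and dosing belong in the protocol, so a separate analysis plan would not be expected to supply the missing rule.

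**What to change.** Replace the any-age wording in the Abstract and section 4 with a numbered minimum-age item in the Inclusion Criteria. Set it so that participants can give their own consent as item 16c requires and are people for whom the fixed regimens are intended. Eighteen years is one possibility; it is an assumption for the sponsor to confirm. Have the IT module, which already takes demographic details before allocating, refuse allocation below that age.

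If minors are intended, state age- or weight-based doses under Interventions (item 11a) and a guardian consent and assent route under item 26a before enrolling any. If the sponsor also wants to cover low-weight adults, a minimum weight can be added in the same amendment.

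The cost is a short amendment and one range check in an existing system. The drawback of an age floor is that younger patients are excluded and the results will not apply to them; how many cannot be said without an age distribution. No sample-size figure changes.

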***SPIRIT Guidance: Background and rationale***

*6a Description of research question and justification for undertaking the trial, including summary of relevant studies (published and unpublished) examining benefits and harms for each intervention*

**Introduction**

Initial warnings that all countries would suffer SARS-Cov-2 (Covid-19) pandemic in 2020 have come true. With mean incubation period reported around 6 to 7 days, the disease is characterized by fever, sore throat, dyspnea, loss of smell and taste that could progress to irreversible damage to lungs leading to death. The global fatality rate of 3 – 4% has been estimated. In the continued absence of a definitive treatment or vaccine, this pandemic continues to harm public health, lifestyles, and economies around the world.

Hydroxychloroquine Sulphate (HQ), commonly used against malaria and rheumatoid arthritis in Indo-Asian region, was reported to stop symptomatic progression of SARS-Cov-2 by inhibiting pH dependent steps of viral replication. It’s effectiveness as monotherapy or in combination with common antibiotics and antivirals is being evaluated around the world. Non-randomized study of Guatret et al promoted the use of macrolides like Azithromycin with HQ in clearing the virus at day 6 among hospitalized patients. None of the 21 patients enrolled in this study reported any adverse drug reactions. Recruitment in HQ arm of ongoing Solidarity Trial resumed after initial concerns of cardiotoxicity were addresses by data safety review. To date, several countries have seen widespread compassionate use of HQ and Azithromycin during the ongoing pandemic.

*6b Explanation for choice of comparators*

Ulrich and Pillat have attributed interest in common antibiotic Azithromycin (Macrolide) to its mechanism of action against rhinovirus - interference with ligand/CD147 receptor interactions and decrease expression of some metalloproteinases (downstream to CD147) that inhibit viral replication. Oseltamivir was one of the earliest drugs tested on SARS-CoV-2 patients in Wuhan, China. With proven effectiveness against influenza viruses, it was evaluated as monotherapy and in combinations to rule out sharing of the same neuraminidase enzyme by novel Coronavirus.

***SPIRIT Guidance:*** *Objectives*

*7 Specific objectives or hypotheses*

**Objectives**

***Primary Objective***

- To evaluate the effectiveness of Hydroxychloroquine Phosphate/Sulfate (200 mg orally 8hr thrice a day for 5 days) versus oseltamivir (75 mg orally twice a day for 5 days) versus Azithromycin (500 mg orally daily on day 1, followed by 250 mg orally twice a day on days 2-5) as monotherapy and in various combinations in clearing the coronavirus nucleic acid from throat and nasal swab and in bringing about clinical improvement on day 7 of follow-up (primary outcomes).

***2.1 Secondary Objectives***

- To evaluate various clinical parameters, quality of life, and symptoms scores, within all randomized participants stratified by subgroups
- To follow up participants not consenting to randomization for the outcomes of SARS-Cov-2 infection with supportive treatment only

**3 STUDY DESIGN**

***SPIRIT Guidance: Study Design***

*8 Description of trial design including type of trial (eg, parallel group, crossover, factorial, single group), allocation ratio, and framework (eg, superiority, equivalence, noninferiority, exploratory)*

An adaptive design, set within a comprehensive cohort study, is chosen because it permits flexibility in this fast-changing clinical and public health scenario. The randomized study will be a multicenter, multiarm, multistage, randomized controlled trial with a parallel design.

***Methods: Participants, interventions, and outcomes***

**4 PARTICIPANTS**

***SPIRIT Guidance: Study setting***

*9 Description of study settings (eg, community clinic, academic hospital) and list of countries where data will be collected. Reference to where list of study sites can be obtained*

Study sites comprise major public-sector tertiary care health facilities and Covid-19 field hospitals being setup within province of Punjab. Hospitals in other provinces and federal areas will also be invited for participation. Households with self-isolating individuals could also participate in the study. A list of hospitals with confirmed participation has been attached as **Annex 3.**

***SPIRIT Guidance:*** *Eligibility criteria*

*10 Inclusion and exclusion criteria for participants. If applicable, eligibility criteria for study centers and individuals who will perform the interventions (eg, surgeons, psychotherapists)*

Eligible will be newly diagnosed patients without any comorbidities or those with controlled chronic medical conditions, e.g. diabetes mellitus and hypertension. Participants of either gender or age group having tested positive for COVID-19 on qRT-PCR (Quantitative Reverse Transcription PCR) will be invited to take part. Participants who are pregnant or lactating, are already taking any treatment, under respiratory distress or severely dyspneic, have liver and kidney failure will be excluded from the study. Each participant will undergo baseline investigation i.e., liver function tests, renal function tests, urinalysis, and Complete Blood Count; at the time of enrollment. However, diagnostic facilities and hospital admission criteria could vary across cities. A case report form (CRF) has been developed for this proposal and **attached** at the end of this document.

